### Inclusion criteria

2.2

1.Aged 50–65 years old2.Naturally menopausal for ≥1year3.Right-handed4.Irregular exercisers (<3 times/week and 30 min/time in the past three months).

### Exclusion criteria

2.3

1.History of major surgery or fracture within the previous 6 months2.Contraindications to exercise, such as severe cardiovascular disease, severe osteoporosis, severe joint inflammation or diagnosed neurological disorders, including but not limited to: stroke, Parkinson's disease, epilepsy, and other neuromuscular diseases3.Presence of metallic foreign bodies in the body4.Inability to understand and complete the test, such as those with cognitive impairment, hearing impairment, or visual impairment

### Randomization and blinding

2.4

Participants meeting the inclusion and exclusion criteria will be randomly assigned to the rTMS + LI-BFRT group, LI-BFRT group, and control group at a 1:1:1 ratio. The randomization sequence will be generated by an independent statistician using a computer program with block randomization to ensure balanced sample sizes across groups throughout the enrollment process. Group allocation results will be concealed in numbered, sealed, opaque envelopes, which are stored and distributed by researchers not involved in recruitment, intervention, or assessment to achieve allocation concealment. Outcome assessors and data analysts will remain blinded to participants' group assignments throughout the study. Researchers implementing the intervention are required to withhold group information during assessments.

### Interventions

2.5

Pre-intervention procedures: Before the intervention, participants in the rTMS + LI-BFRT and LI-BFRT groups underwent a one-repetition maximum (1RM) test and arterial occlusion pressure (AOP) measurement, and were trained to use the 6–20 Borg Rating of Perceived Exertion (RPE) scale to determine target resistance loads. Exercise loads were applied using appropriately weighted dumbbells. Missed sessions were rescheduled within the same week to maintain consistent intervention volume. All participants attended a pre-intervention orientation to familiarize themselves with the procedures.

Adherence and fidelity: All sessions were supervised by trained researchers. Attendance and completion of prescribed exercise sets were recorded digitally. Any missed sessions or protocol deviations were documented. Adherence was calculated as the percentage of completed sessions relative to the total prescribed, with an attendance rate of ≥ 80% considered a valid indicator of intervention effectiveness. Detailed intervention protocols for all groups are provided in Table 2.

**Table 2 T2:** Details of the three groups of protocol.

Weeks	Group	Specific intervention content	Sets	Repetitions	Interval rest time between sets	Intensity	Frequency
1–4	LI-BFRT	Seated biceps curl, Seated shoulder press Seated knee extension, Squat	4	12, 10, 10, 10	30s	Phase 1 20%1RM	3times/week
	rTMS + LI-BFRT	M1 area, at 10 Hz, 90%RMT, intermittent stimulation, a total of 2,000 pulses; LI-BFRT immediately after the stimulation ends.					
	CG	Education session (20 min)	/	/	/	/	1time/week
5–8	LI-BFRT	Seated biceps curl, Seated shoulder press Seated knee extension, Squat	4	12, 10, 10, 10	30s	Phase 2 25%1RM	3times/week
	rTMS + LI-BFRT	M1 area, at 10 Hz, 90%RMT, intermittent stimulation, a total of 2,000 pulses; LI-BFRT immediately after the stimulation ends					
	CG	Education session (20 min)	/	/	/	/	1time/week
8–12	LI-BFRT	Seated biceps curl, Seated shoulder press Seated knee extension, Squat	4	12, 10, 10, 10	30s	Phase 3 30%1RM	3times/week
	rTMS + LI-BFRT	M1 area, at 10 Hz, 90%RMT, intermittent stimulation, a total of 2,000 pulses; LI-BFRT immediately after the stimulation ends					
	CG	Education session (20 min)	/	/	/	/	1 time/week
M1 area: primary motor cortex							

#### LI-BFRT

2.5.1

Participants will undergo a 12-week intervention consisting of 3 sessions per week, each lasting 40 min, using LI-BFRT (with dumbbells and leg sandbags as resistance load forms). The 40-min intervention includes a 5-min warm-up under the guidance of an instructor, a 30-min formal intervention, and a 5-min cool-down. According to the study by Cook et al. (37), the load is set at 20%–30% of the estimated 1RM, with 4 sets (12-10-10-10), 30 s of rest between sets, and 1 min of rest between training intervals. The four resistance exercises included two upper-body exercises: seated biceps curl and seated shoulder press; and two lower-body exercises: seated knee extension and squat.

The estimated 1RM is calculated using the maximum number of repetitions and the second-maximum load to determine the load for resistance training. First, the subject is given an appropriate load and asked to perform as many repetitions as possible. If they can perform more than 10 repetitions, they rest for 3 min and then attempt the same exercise with a heavier weight. When the maximum number of repetitions is 10 or fewer, the load is considered the second-maximum load. The formula for estimating 1RM is as follows (38):$$\begin{array}{rl} 1\mathrm{RM}\; & =\;\mathrm{Submaximal}\;\mathrm{load}\;(\mathrm{kg})/(102.78-2.78\\ & \;\times \;\mathrm{Maximum}\;\mathrm{number}\;\mathrm{of}\;\mathrm{repetitions})/100 \end{array}$$During training, inflatable cuffs (Theratools®, Germany) are placed on the proximal limbs, and individualized AOP will be determined before the intervention begins. A Doppler ultrasound imaging diagnostic device was used to detect the AOP of the upper and lower limbs. The compression cuffs were placed on the proximal parts of the participants' upper arms and thighs. Subsequently, the ultrasound probe was placed on the radial artery of the upper limb and the tibial artery of the lower limb. The cuff was inflated until the arterial pulse disappeared and no arterial blood flow was detected by the ultrasound probe, and the pressure at this time was the AOP. The compression intensity of the cuff was set at 60% of the AOP (39).

#### rTMS+LI-BFRT

2.5.2

Participants will undergo a 12-week intervention consisting of three sessions per week, each lasting 60 min, combining rTMS (20 min) and LI-BFRT (40 min). The rTMS protocol is as follows: stimulation intensity of 90% of the RMT, is applied to the primary motor cortex (M1) with a stimulation frequency of 10 Hz, each sequence lasting 10 s, and an interval of 50 s. A total of 1,000 pulses are administered to each hemisphere, resulting in a total of 2,000 pulses for the rTMS intervention. Immediately thereafter, the same exercise intervention as the LI-BFRT group was performed.

The RMT will be determined before the start of the intervention. Measurements and interventions were performed using a MagTD transcranial magnetic stimulator (Irid Medical Equipment New Technology Co., Ltd., Wuhan, China) equipped with an aimQ tracking navigation system. Signals will be amplified and band-pass filtered between 20 Hz and 1 kHz, with a sensitivity of 200 μV/div and a sampling rate of 5 kHz. Subjects were instructed to maintain complete relaxation of the target muscle during stimulation and confirm the absence of background activity via real-time EMG feedback. First, activate the MEPs monitoring module. Surface electromyography (EMG) of the abductor pollicis brevis muscle is recorded using dedicated electrode wires. Align the center of the “8-shaped” coil with the representative region of the cerebral cortex associated with the hand function, ensuring the coil is tangent to the skull surface at a 45° angle. Subsequently, sTMS to observe reactive movements in the affected fingers. The RMT is defined as the minimum magnetic stimulation intensity required to elicit MEPs greater than 50 μV in at least 5 out of 10 consecutive sTMS stimuli while the thenar muscle is in a relaxed state.

#### Control group

2.5.3

Participants in the control group will not undergo any exercise intervention and will maintain their original lifestyle habits. However, they will participate in a 12-week health education course, once a week for 20 min per session, to learn about skeletal muscle and exercise health.

### Outcome assessment

2.6

#### Primary outcome

2.6.1

##### Muscle cross-sectional area (CSA)

2.6.1.1

CSA is diagnosed by an experienced radiologist. Lower limb muscle cross-sectional area is measured using a CT spiral scanner (uCT520, United Imaging Medical Technology Co., Ltd, Shanghai, China). Patients are instructed to lie in a supine position, ensuring that the CT scan plane is perpendicular to the coronal plane of the lower limbs. The scanning regions include: the thigh muscle cross-sectional area, the midpoint of the line connecting the greater trochanter of the femur and the lateral condyle of the femur (40), the calf muscle cross-sectional area, the midpoint and the upper third of the line connecting the inferior border of the patella and the lateral malleolus (41).

##### Muscle strength

2.6.1.2

Grip strength, which represents upper limb strength, was measured using a handheld grip dynamometer (JAMAR smart, USA). Participants sat with their elbows flexed at 90° and their upper limbs immobilized while holding the grip dynamometer. Upon receiving the “start” command, they gripped the inner and outer handles with maximum force, and the peak grip strength was recorded. Three measurements were taken for each hand. There was a one-minute interval between each measurement, and the final result was the maximum value of the three measurements. Measure the maximal voluntary contraction (MVC) of knee extension of the lower limbs using a portable muscle strength tester, micro FET3 (Hoggan Health Industries, USA). During the test, the subject sat on a chair or bed with both feet suspended in the air, the hip and knee joints flexed at 90°, and the tester held the device in front of the subject's lower leg near the ankle joint. Upon the “start” command, the participant performed knee extension with maximum force, while the tester applied resistance using the portable muscle strength tester micro FET3 for 4 s, recording the peak muscle strength.

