**Figure 1 F1:**
[figure not shown]
Flow chart showing the participant recruitment, intervention and assessment process. LI-BFRT, low intensity-blood flow restriction training; rTMS, repetitive transcranial magnetic stimulation; 1RM, 1 repetition maximum.

This study recruited healthy postmenopausal women. After applying inclusion and exclusion criteria, eligible participants were randomly assigned to the rTMS + LI-BFRT group, LI-BFRT group, and control group in a 1:1:1 ratio. Researchers confirmed the basic information of all participants who had signed informed consent forms (age, date of birth, contact information); after confirmation, blood samples were collected from participants, and height, weight, and body composition were measured. Subsequently, tests were conducted to assess skeletal muscle mass, skeletal muscle strength, motor cortex excitability, and motor performance. Participants in the two intervention groups received a 12-week supervised training intervention, three times per week. The control group was instructed to maintain their previous lifestyle and undergo a 12-week health education program, once per week. The program comprises weekly lectures on general health topics (nutrition, sleep hygiene, chronic disease awareness) and explicitly does not include active physical training or exercise prescriptions. All participants were assessed at three time points: pre-intervention (Week 0), post-intervention (Week 12), and at long-term follow-up (Week 24). The intervention and assessment schedule are outlined in Table 1.

**Table 1 T1:** The schedule of participant recruitment, intervention, and study assessment.

Variables	Recruitment and screening	Baseline assessment	Intervention (Week 1-Week12)		Follow-up assessment	Long-term Follow-up assessment
Time-point		Week 0	Week 4	Week 8	Week 12	Week 24
Information consent	X					
Inclusion and exclusion criteria	X					
Demographic data	X					
Randomization	X					
AOP test		X				
RMT test		X				
Resistance training load		X	X	X		
Primary outcomes						
Thigh muscle CSA		X			X	X
Calf muscles CSA		X			X	X
Hand grip strength		X			X	X
Knee extension MVC		X			X	X
Secondary outcome						
Body composition		X			X	X
5-times chair stand test		X			X	X
30-Second Chair Stand test		X			X	X
Timed Up and Go test		X			X	X
30-Second Arm Curl Test		X			X	X
MEPs test		X			X	X
Hematological parameters		X			X	X

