###### 5-time sit-to-stand test

2.6.2.2.1

Participants sit on a chair without armrests (height: 45 cm), with both feet flat on the ground, back not leaning against the chair back, and hands crossed over the chest. Upon hearing the “start” command, they perform 5 repetitions of standing up (with knees fully extended when standing) and sitting down as quickly as possible. The time taken to complete the 5 repetitions is recorded (in seconds). The test is conducted three times, with a 1-min rest interval between each trial. The average of the three test times is used as the final result.

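### Primary knee-extension strength is taken against a tester-held dynamometer with no fixed pad position and no repeat rule, which can cap measured gains and adds avoidable noise

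*Protocol article*

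**What the plan says.** Table 1 of the protocol article lists "Knee extension MVC" among the primary outcomes, assessed at Weeks 0, 12 and 24. It is the only lower-limb strength measure among them; the others are thigh CSA, calf CSA and grip.

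Section 2.6.1.2 (Muscle strength) describes the test. On position: "the subject sat on a chair or bed with both feet suspended in the air". On fixation and placement: "the tester held the device in front of the subject's lower leg near the ankle joint". On resistance and the recorded value: "the tester applied resistance using the portable muscle strength tester micro FET3 for 4 s, recording the peak muscle strength". The section mentions no strap or frame, no marked pad distance, no lever arm or torque conversion, no number of trials and no aggregation rule.

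For grip, the same section specifies three measurements per hand and adds: "There was a one-minute interval between each measurement, and the final result was the maximum value of the three measurements". For a secondary test, section 2.6.2.2.1 (5-time sit-to-stand test) specifies three attempts: "The average of the three test times is used as the final result".

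Section 2.4 states that outcome assessors are blinded to group.

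**The concern.** Three features of the method matter, and they act differently.

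- **Tester-held resistance.** The device reads at most what the tester can resist. A woman stronger than the tester is recorded at about the tester's limit. Both active arms train seated knee extension and squat for 12 weeks, so training moves women towards that limit. Any cap then trims the trained arms more than the control arm and pulls the estimated difference towards zero. Blinding does not prevent this, because the cap depends on the participant's strength and not on knowledge of her arm.
- **Pad position.** Near the ankle is a region and not a point. For the same knee torque, force varies inversely with distance from the knee, so a different placement at Week 12 changes the reading with no change in strength.
- **Repeats.** No repeat rule is given, although grip and a secondary test both have one. If one trial is done, its full noise enters the outcome.

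At stake are a possible underestimate of the training effect on this primary outcome and a loss of precision that could cheaply be avoided.

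**Working it through.** The plan gives no figure for this measurement, so there is none to reproduce. The inputs below are assumptions chosen to show the range.

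**1. Ceiling.** Assume true force X is normal with SD s = 60 N and mean m = 250 N at baseline. After a 15% gain (37.5 N) the mean is 287.5 N. With tester limit L, the recorded value is min(X, L). Writing a = (L − m)/s,

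E[min(X, L)] = m·Φ(a) − s·φ(a) + L·(1 − Φ(a)).

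Worked for L = 300 N:

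- Before: a = 0.833, giving 250 × 0.7977 − 60 × 0.2819 + 300 × 0.2023 = 243.2 N.
- After: a = 0.208, giving 287.5 × 0.5825 − 60 × 0.3904 + 300 × 0.4175 = 269.3 N.
- Observed gain: 26.1 N, or 26.1/37.5 = 70% of the truth.

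The standardised effect divides the observed gain by the root mean square of the two capped SDs. Without a cap it is 37.5/60 = 0.625.

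| Tester limit (N) | Observed gain (N) | Share of mean gain kept | Standardised effect |
|---|---|---|---|
| 270 | 19.1 | 51% | 0.53 |
| 300 | 26.1 | 70% | 0.58 |
| 330 | 31.6 | 84% | 0.61 |
| 360 | 35.0 | 93% | 0.62 |
| 400 | 36.9 | 98% | 0.63 |

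The standardised effect falls less than the mean gain because the cap also shrinks the spread. The result also depends on how strong the women are. With baseline 200 N, SD 50 N and a 15% gain, limits of 300 and 330 N keep 95% and 99%.

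For the contrast between the two trained arms, suppose rTMS adds a further 12.5 N (assumed). The same formula with means 287.5 and 300 N keeps 35%, 54% and 73% of that difference at limits of 270, 300 and 330 N, and 96% at 400 N. On these inputs the cap acts more strongly there than on trained versus control.

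**2. Pad position.** At constant torque, moving the pad d cm towards the knee on a lever of l cm changes force by l/(l − d) − 1. With l assumed to be 32-38 cm:

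- d = 2 cm: 38/36 − 1 = 5.6% to 32/30 − 1 = 6.7%.
- d = 3 cm: 38/35 − 1 = 8.6% to 32/29 − 1 = 10.3%.

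These are shifts in one woman's reading at one visit. They are not shifts in a group mean.

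**3. Repeats.** Assume a within-session error SD of 10%. The SD of the maximum of three independent trials is then about 7.5% (simulated). Set against the between-woman SD of 60/250 = 24%, the total SD at one visit falls only from √(24² + 10²) = 26.0% to √(24² + 7.5²) = 25.1%. For a change between two visits, the error part falls from √2 × 10 = 14.1% to √2 × 7.5 = 10.6%, so the benefit is larger there.

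**The case against.** **One trial is not stated.** A reader might infer that knee extension is done once. The text walks through one execution and gives no count. The grip description opens in a similar way and then adds its repeat rule; leaving that sentence out for knee extension is silence. A journal article may leave trial counts to the full protocol. This objection stands: a single trial is only the natural reading, and the single-trial cost is conditional on it. Likewise, the text speaks of peak strength without a unit, so an analysis of raw force is inferred from the absence of any lever arm.

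**Noise is not bias.** A reader might also infer that pad and trial error pull the comparison towards no effect, as the ceiling does. They do not. With randomised allocation and blinded assessors, such error should be about equal across arms. It widens the spread of a continuous outcome and leaves the expected difference in means unchanged. A 2-3 cm shift in individuals also largely averages out of a group mean.

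**The ceiling is hypothetical.** Every force value above is assumed. At a 270 N limit, 37% of women would already exceed the tester at baseline; at 360-400 N little is lost. This stands as a limit on size.

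**Tester-held testing is a coherent method, and this is one of four primary measures.** Both statements are true. But hand fixation and the loose pad position are stated method and not gaps left by condensing, and a better arrangement with the same device is cheap.

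**Conclusion.** The point holds in limited form. The protocol fixes tester-held resistance and an unmarked pad position for a primary outcome, and gives no repeat rule where it gives one for grip. Only the ceiling can bias the result, and only if trained women reach the tester's limit. On the assumed 250 N baseline, SD 60 N and 37.5 N gain, the mean gain kept is 51-84% at limits of 270-330 N and 93-98% at 360-400 N. The standardised effect goes from 0.625 to 0.53-0.61 over the lower range. Pad placement (about 6-10% in an individual reading for 2-3 cm) and, if it applies, single-trial noise cost precision only.

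The documents do not support saying that the test is definitely a single effort, that all three features bias the contrasts, or that the ceiling is known to be large. The likely loss runs from material to negligible and cannot be narrowed without the testers' limits and the participants' forces.

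**What to change.** In section 2.6.1.2:

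1. Anchor the same dynamometer to the chair or bed with a non-elastic strap, so that the tester no longer supplies the resistance.
2. Measure and record the pad's distance from the knee joint line at Week 0, reuse it at Weeks 12 and 24, and analyse torque (force × distance).
3. Apply the rule already used for grip: three trials, one-minute rests, maximum kept.
4. Use one method at all visits for each participant. Where a baseline has already been taken tester-held, keep that method for that participant and at least reuse the pad distance if it was recorded.

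Repeats alone would not be enough: they reduce within-session noise but leave the tester's limit and the pad position untouched.

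The cost is a strap, a tape measure, a few more minutes per visit and slightly more effort for participants. The device and the assessor stay the same.

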#### Secondary outcomes

2.6.2

##### Body composition

2.6.2.1

Body composition was measured using a body composition analyzer (Inbody S10, Korea). Participants should remain normally hydrated before testing. After cleaning their hands and feet, participants stand on the device's electrode plate, ensuring that both feet are precisely aligned with the electrodes, with the heels placed on the origin mark. Participants are instructed to hold the handle with their thumbs touching the oval electrode pads and their four fingers wrapped around the handle, with both arms extended at a 45° angle and kept straight. Throughout the test, participants are required to remain still and avoid moving their limbs or talking. The BIA device will automatically measure participants' body fat, body fat percentage, lean body mass, and visceral fat.

##### Physical performance

2.6.2.2

###### 5-time sit-to-stand test

2.6.2.2.1

Participants sit on a chair without armrests (height: 45 cm), with both feet flat on the ground, back not leaning against the chair back, and hands crossed over the chest. Upon hearing the “start” command, they perform 5 repetitions of standing up (with knees fully extended when standing) and sitting down as quickly as possible. The time taken to complete the 5 repetitions is recorded (in seconds). The test is conducted three times, with a 1-min rest interval between each trial. The average of the three test times is used as the final result.

###### 30-second stand test

2.6.2.2.2

Participants sit on a chair without armrests (height: 45 cm), with their feet flat on the ground, their backs not leaning against the backrest, and their hands crossed in front of their chests. Upon hearing the command “start,” they perform the actions of standing up (with knees fully extended) and sitting down as quickly as possible. The number of times the participant completes the actions within 30 s is recorded.

###### Timed up-and-go test

2.6.2.2.3

Participants are required to stand up from a chair with armrests at a height of approximately 45 cm, walk in a straight line for 3 m, turn around, return, and sit down. The tester uses a stopwatch to record the total time from the start to when the participant is fully seated.

###### 30-second arm curl test

2.6.2.2.4

Participants sits on a straight-backed chair (height: 45 cm), with both feet flat on the ground, the back firmly against the chair back, and the non-test arm hanging naturally or resting lightly on the thigh. The tested arm holds a 2-kg dumbbell, with the arm fully extended and naturally hanging at the side of the body. Upon hearing the “start” command, using the elbow joint as a pivot point, quickly raise the dumbbell to shoulder height, then slowly lower it. Throughout the movement, the arm must not touch the thigh. Continue for 30 s. Record the number of correct repetitions completed.

